## Abstract

**Background:**

Surgical resection is a mainstay to treat hepatocellular carcinoma (HCC) with portal vein tumor thrombus (PVTT) in east Asia. However, the postoperative recurrence rate is high. It is necessary to explore neo-adjuvant therapy to increase the surgical resection rate and improve overall survival. Evidence has shown that lenvatinib combined with PD-1 inhibitors is safe and effective in the treatment of advanced unresectable HCC. Radiotherapy is also an effective treatment method for PVTT and has a synergistic effect in combination with PD-1 inhibitors. Surgical resection after Lenvatinib and sintilimab combined with radiotherapy as a neoadjuvant treatment regimen may be a new exploration of HCC with PVTT, but there were not any reported.

**Methods:**

This open-label, single-arm, prospective, multi-center Phase I trial will enroll 20 HCC patients with PVTT who have a resectable primary tumor and no extra-hepatic metastasis. Eligible patients will be given radiotherapy, 3Gy*10 fraction, and will receive lenvatinib 8-12mg once daily and sintilimab 200mg once every three weeks. Surgical resection will be performed 6-8 weeks after radiotherapy. The primary endpoint is safety (number of patients ≥3G TRAE) and the number of patients who complete pre-op treatment and proceed to surgery. The secondary study endpoints include Major Pathological Response (MPR), 1-year tumor recurrence-free rate, Objective Response Rate (ORR), Imaging-Pathology Concordance Rate (IPCR), PVTT regression rate, Median Overall Survival (OS) and Recurrence Free Survival (RFS).

**Discussion:**

This trial may confirm that surgical resection following intensive neoadjuvant therapy can provide a safe and efficient regimen for BCLC stage C patients with PVTT.

**Clinical trial registration:**

https://clinicaltrials.gov/, identifier (NCT05225116).

## Introduction

Portal vein tumor thrombus (PVTT), having biological behavior of vascular invasion, is common in patients who are first diagnosed with hepatocellular carcinoma (HCC). The incidence of PVTT varies between countries and regions, ranging from 13% to 45% (1). HCC patients with PVTT have a worse prognosis, with a median survival of only 4-6 months given the best supportive care (2, 3). The management guidelines of HCC in the United States and ESMO recommend sorafenib and Lenvatinib as first line systemic therapy for PVTT patients (4, 5). However, the efficacy is modest. Guidelines for the management of HCC in Asia, such as Asian-Pacific guidelines (6) and guidelines in mainland China (7), Korea (8), and Taiwan (9), suggest that local therapies (hepatic resection, radiotherapy, TACE, and HAIC for example) are optional regimen for patients with PVTT. A real-world study in Japan reported postoperative recurrence-free survival according to the degree of PVTT as follows: Vp1, 1.23 years; Vp2, 0.82 years; Vp3, 0.56 years and Vp4, 0.38 years (10). The clinical benefit is unsatisfactory either. Till now, there is no global consensus or standard guidelines for the treatment of HCC patients with PVTT, along with an urgency to find new treatments.

Recently, immunotherapy marks a new dawn in HCC management. IMbrave 150 study demonstrated an improvement in clinical benefit with atezolizumab (anti-PDL1 antibody) and bevacizumab (anti-VEGF antibody). According to IMbrave 150, 129 patients with macrovascular invasion included in the study had mOS of 14.2 months vs. 9.7 months (HR 0.68)) and mPFS of 6.7 months vs. 4.2 months (HR 0.59), which confirmed the effectiveness of ICIs combined with VEGF inhibitor in patients with PVTT. However, in 73 patients with Vp4 PVTT, the OS was 7.6 months, which is still unsatisfactory (11). In a prospective study by Lu et al., examined the efficacy of PD-1 inhibitors combined with Lenvatinib in HCC patients with major vascular invasion as conversion therapy. Successful conversion rate was 42.4%; median overall survival was 6.5 months (12).

Radiotherapy is increasingly used in advanced HCC and demonstrated encouraging clinical benefit in management of PVTT. Cheng et al. found that neoadjuvant radiotherapy reduced the extent of PVTT and improved post-operative survival rate reaching 75.2% at 12 month (13). In addition, radiotherapy upregulated PD-L1 in patients with HCC, potentiated the antitumor effect of immune checkpoint inhibitors and augmented cytotoxic T-cell infiltration in HCC tumors in immunocompetent mice (14).

Thus, we designed this study to evaluate the safety and efficacy of radiotherapy combined with lenvatinib plus PD-1 inhibitors as neo-adjuvant therapy in hepatocellular carcinoma with portal vein thrombus.

## Methods and analysis

### Study design

This is an open-label, single-arm, prospective, multi-center phase I trial in HCC patients with portal vein thrombus which will be conducted in 5 hospitals in China. (**Figure 1**). The study is being followed the Declaration of Helsinki and Good Clinical Practice. The protocol and its amendments have been approved by the ethics committee of Beijing Tsinghua Changgung Hospital (No. 21323-0-03). The recruitment started on December 01, 2022. The enrolment is estimated to complete in December 1, 2025.

**Figure 1 f1:**
[figure not shown]
Study design.

### Selection of subjects

#### Eligibility criteria

The patient inclusion and exclusion criteria are detailed in **Table 1**.

**Table 1 T1:** Eligibility criteria.

Inclusion criteria	
1	Aged 18-70 years, no gender restrictions
2	Been diagnosed with HCC by histopathological or cytological examinations or meet the Chinese clinical diagnostic criteria of the "Guidelines for the Diagnosis and Treatment of Primary Liver Cancer" (2019 Edition)
3	Tumor thrombus in the main portal vein or branches (vp1, vp2, vp3 or vp4 of Japanese PVTT type) and without extrahepatic metastasis
4	The primary tumor is resectable: the remaining liver vascular structure is intact and the liver volume is sufficient, which is in line with the decision-making system for safe hepatectomy
5	ECOG performance status 0-1
6	Child-Pugh score ≤7
7	HBV DNA <500 IU/ml and have been receiving conventional antiviral therapy for HBV antigen-positive patients
8	For normal function of major organs, the following criteria should be met: Adequate bone marrow function, defined as: Absolute neutrophil count (ANC ≥1.5 x 10^9 /L); Hemoglobin (Hb ≥8.5 g/dL) ; Platelet (PLT ≥ 75 x 10^9/L) Adequate liver function, defined as: Albumin ≥ 2.8 g/dL, Bilirubin ≤3.0 mg/dL, Aspartate aminotransferase (AST), alkaline phosphatase (ALP) and alanine aminotransferase (ALT) were ≤ 5 times the upper limit of normal (ULN) Adequate coagulation function, defined as: International Normalized Ratio (INR) of 2.3 or less Adequate renal function, defined as: creatinine clearance > 40 mL/min, calculated according to the Cockcroft and Gault formula Adequate pancreatic function, defined as: amylase and lipase ≤ 1.5 times ULN
9	Adequate blood pressure (BP) control with up to 3 antihypertensive drugs, defined as: BP ≤150/90 mmHg at screening, and there is no change for antihypertensive therapy within 1 week prior to Cycle 1/Day 1
10	The patient is expected to survive more than 3 months
11	No pregnancy or planned pregnancy
12	Witten informed consent

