**Exclusion criteria**	
1	Extrahepatic metastasis
2	Diffuse liver cancer
3	Patients who have received targeted drugs and immune checkpoint inhibitors in the past
4	Hypersensitivity to lenvatinib or PD-1 inhibitor components
5	Patients with myocardial ischemia or myocardial infarction of grade II or above, and poorly controlled arrhythmias (including QTc interval ≥ 470 ms); according to the NYHA standard, grade III to IV cardiac insufficiency, or cardiac color Doppler ultrasonography indicates left ventricular ejection Blood fraction (LVEF) <50%
6	Abnormal coagulation function : INR>1.5 or prothrombin time (PT) > ULN + 4 seconds or activated partial thromboplastin time (APTT) >1.5 ULN, with bleeding tendency or receiving thrombolytic or anticoagulation therapy
7	Pregnant or breastfeeding women; patients with childbearing potential who are unwilling or unable to take effective contraceptive measures
8	Have a history of mental illness or abuse of psychotropic substances
9	Combined HIV-infected
10	History of liver resection, liver transplantation, interventional therapy, and other malignant tumors
11	Patients with active infection
12	With contraindications to radiotherapy
13	Patients with poor compliance such as floating population
14	Those who have participated in clinical trials of other experimental drugs or devices within four weeks
15	Those deemed unsuitable for inclusion by the investigator

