#### Interventional methods

Eligible patients will receive radiotherapy for PVTT and primary tumor. CT simulation localization will be performed before radiotherapy and the CT scan images will be transmitted to the treatment planning system in preparation for target delineation. The gross tumor volume will include liver tumor lesions and portal vein tumor thrombus displayed on the CT image. The clinical target volume margin will be 0.5cm for the liver tumor lesions and no expansion for portal vein tumor thrombus lesions. The interfractional margin will be set at 0.5cm and combined with internal motion compensation to form a field-specific planning treatment volume. RT dose is 30Gy (3Gy*10fractions). RT will be given from Monday to Friday, and will be finished in two weeks. Lenvatinib is started on the first day of radiotherapy (daily dose determined according to body weight, 8mg for bodyweight < 60 kg and 12 mg for bodyweight ≥ 60 kg) and will be discontinued 7 days before surgery.

The PD-1 inhibitor(sintilimab) is also started on the first day of radiotherapy, with a fixed dose of 200 mg every three weeks for three cycles. Surgery will be performed 6 to 8 weeks after radiotherapy (**Figure 2**). Dose adjustment, interruption, or discontinuation of lenvatinib and sintilimab according to the adverse events (AES) is detailed in **Tables 2**, **3**.

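### Table 1 gives two inconsistent INR limits (2.3 in inclusion 8, 1.5 in exclusion 6), and the closing clause of exclusion 6 has no clear scope

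*Protocol article*

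**What the plan says.** All the relevant text is in Table 1 of the Protocol article (Eligibility criteria).

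- Inclusion 8, on organ function, counts coagulation as adequate at an "International Normalized Ratio (INR) of 2.3 or less". It sets no PT or APTT limit.
- Exclusion 6 begins "Abnormal coagulation function : INR>1.5 or prothrombin time (PT) > ULN + 4 seconds" and continues, after a further or, with "activated partial thromboplastin time (APTT) >1.5 ULN, with bleeding tendency or receiving thrombolytic or anticoagulation therapy".

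Three other items bear on fitness for treatment. Inclusion 4 requires a resectable primary tumour, "which is in line with the decision-making system for safe hepatectomy". Inclusion 6 requires "Child-Pugh score ≤7". Exclusion 15 removes "Those deemed unsuitable for inclusion by the investigator". None of them states a limit for INR, PT or APTT, or a rule on anticoagulants.

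On setting, Study design describes a trial "which will be conducted in 5 hospitals in China". Under Interventional methods, lenvatinib starts on the first day of radiotherapy and "will be discontinued 7 days before surgery".

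**The concern.** An INR of 1.8 counts as adequate in one row of Table 1 and is listed as abnormal in another. Which row decides depends on what the last clause of exclusion 6 attaches to. It follows a comma after three laboratory limits joined by or, and could qualify all three, qualify APTT only, or add further exclusions of its own.

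Five hospitals must apply this text. Two of them could reach different decisions on the same patient and both be following the protocol. The patients concerned would take lenvatinib and then undergo hepatectomy. Table 2 names bleeding as a reason to suspend or stop lenvatinib, and the primary safety endpoint counts patients with treatment-related events of grade 3 or worse. Coagulation status at entry is therefore a criterion that the sites should apply in the same way.

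**Working it through.** The plan has no figure to reproduce here, and no sample size, power or error rate enters. The check combines the two items under the usual rule that a patient must meet every inclusion criterion and no exclusion criterion.

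**Inputs.** Inclusion 8: INR ≤2.3. Exclusion 6: Lab = INR >1.5, or PT > ULN + 4 s, or APTT >1.5 ULN; Bleed = bleeding tendency; Drug = thrombolytic or anticoagulant therapy.

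**Readings of exclusion 6 that the grammar allows.**

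- R1: every listed item excludes on its own (Lab or Bleed or Drug).
- R2: the clause qualifies all the laboratory limits: Lab and (Bleed or Drug).
- R3: only bleeding tendency qualifies the limits, and treatment stands alone: (Lab and Bleed) or Drug.
- R4: INR or PT excludes alone, and the clause qualifies APTT only.

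**Test patients** (PT and APTT within limits):

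| Patient | R1 | R2 | R3 | R4 |
|---|---|---|---|---|
| INR 1.8, no Bleed, no Drug | excluded | eligible | eligible | excluded |
| INR 1.2, on an anticoagulant | excluded | eligible | excluded | eligible |
| INR 1.8, on an anticoagulant | excluded | excluded | excluded | excluded |
| INR 1.8, bleeding tendency | excluded | excluded | excluded | excluded |
| INR above 2.3 | excluded (inclusion 8) | excluded | excluded | excluded |

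**What follows.**

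1. Under R1 and R4, INR >1.5 excludes alone. The conditions INR ≤2.3 and INR ≤1.5 then reduce to INR ≤1.5, so the limit in inclusion 8 never acts.
2. Under R2 and R3 the two items are compatible. Patients in the band of width 2.3 − 1.5 = 0.8 may enrol if they have no bleeding tendency and no such therapy.
3. R2 and R4 admit an anticoagulated patient with normal tests; R1 and R3 do not.
4. Under R2 and R3, a patient with neither bleeding tendency nor such therapy has no APTT ceiling, because inclusion 8 limits only INR. The same holds under R4.

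The first two rows of the table are the ambiguous groups. They are distinct: one is defined by INR without the clinical features, the other by treatment without abnormal tests. No other section of the article says which reading applies.

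**The case against.** The strongest reply is that the criteria can be applied as they stand. If INR >1.5 excludes alone, 1.5 governs and the 2.3 is merely redundant. If the clause qualifies the limits, the items form a sensible two-tier rule: a general ceiling of 2.3, and 1.5 for patients at added risk. This stands in part. A reader might infer that eligibility is undefined, and that goes too far, since each reading gives a definite answer. What fails is the step from each reading being workable to the text having chosen one. Under the first reading the inclusion limit is an error; the second is nowhere stated.

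A second reply is that resectability, the Child-Pugh limit, the platelet minimum in inclusion 8 and investigator judgement will screen many of these patients. That is fair and reduces the practical consequence. It does not fix an INR or anticoagulant rule, and case-by-case judgement does not make five sites consistent.

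A third reply is that this is a journal article and the full protocol may be clearer. That could settle the scope of the clause. It would not explain why two different INR values are printed in the same table, and that is the core of the point.

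Finally, the harm is not demonstrated. Patients in the first ambiguous group have, by definition, no bleeding tendency and no anticoagulant, and the bleeding rule in Table 2 is a general dose rule that the article does not tie to baseline INR. This is correct and limits the weight of the point.

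**Conclusion.** The inconsistency is real and stands on the printed text: two INR limits in one table, with no statement of which governs and no clear scope for the closing clause of exclusion 6. Eligibility depends on the reading for two separate groups: INR above 1.5 and up to 2.3 without bleeding tendency or thrombolytic or anticoagulant therapy, and patients on such therapy with normal coagulation tests.

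Two stronger conclusions might be drawn, and the document supports neither. One is that anticoagulated patients with an INR in the disputed band are left in doubt; they are excluded under all four readings. The other is that the wording will cause bleeding or bias the safety endpoint. The article does not say how many patients fall in either group, so that effect cannot be sized.

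The impact is minor to moderate: possible bleeding risk and inconsistent enrolment across five hospitals. Sample size, error rates and analysis are unaffected. The conclusion assumes the usual rule for combining inclusion and exclusion criteria, and that Table 1 reflects the criteria the sites use.

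**What to change.** Use one INR limit in both items. The conservative choice before lenvatinib and hepatectomy is to change inclusion 8 to INR ≤1.5 and to split exclusion 6 into three exclusions that each apply alone:

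- INR >1.5, PT > ULN + 4 s, or APTT >1.5 ULN;
- bleeding tendency;
- current thrombolytic or anticoagulant therapy.

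Whether 1.5 is right, and whether every anticoagulated patient should be excluded, are clinical decisions that the document does not dictate. If a two-tier rule was intended, write it out: INR ≤2.3 in general and ≤1.5 for patients with bleeding tendency or on such therapy, with PT and APTT limits for each tier.

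The cost is a wording amendment to two items and, with a single limit of 1.5, possibly a few fewer eligible patients. Recruitment began on December 01, 2022, so the amendment comes after patients may have been enrolled under the present wording. The sponsor should record which reading each site has used so far.

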**Exclusion criteria**	
1	Extrahepatic metastasis
2	Diffuse liver cancer
3	Patients who have received targeted drugs and immune checkpoint inhibitors in the past
4	Hypersensitivity to lenvatinib or PD-1 inhibitor components
5	Patients with myocardial ischemia or myocardial infarction of grade II or above, and poorly controlled arrhythmias (including QTc interval ≥ 470 ms); according to the NYHA standard, grade III to IV cardiac insufficiency, or cardiac color Doppler ultrasonography indicates left ventricular ejection Blood fraction (LVEF) <50%
6	Abnormal coagulation function : INR>1.5 or prothrombin time (PT) > ULN + 4 seconds or activated partial thromboplastin time (APTT) >1.5 ULN, with bleeding tendency or receiving thrombolytic or anticoagulation therapy
7	Pregnant or breastfeeding women; patients with childbearing potential who are unwilling or unable to take effective contraceptive measures
8	Have a history of mental illness or abuse of psychotropic substances
9	Combined HIV-infected
10	History of liver resection, liver transplantation, interventional therapy, and other malignant tumors
11	Patients with active infection
12	With contraindications to radiotherapy
13	Patients with poor compliance such as floating population
14	Those who have participated in clinical trials of other experimental drugs or devices within four weeks
15	Those deemed unsuitable for inclusion by the investigator

#### Interventional methods

Eligible patients will receive radiotherapy for PVTT and primary tumor. CT simulation localization will be performed before radiotherapy and the CT scan images will be transmitted to the treatment planning system in preparation for target delineation. The gross tumor volume will include liver tumor lesions and portal vein tumor thrombus displayed on the CT image. The clinical target volume margin will be 0.5cm for the liver tumor lesions and no expansion for portal vein tumor thrombus lesions. The interfractional margin will be set at 0.5cm and combined with internal motion compensation to form a field-specific planning treatment volume. RT dose is 30Gy (3Gy*10fractions). RT will be given from Monday to Friday, and will be finished in two weeks. Lenvatinib is started on the first day of radiotherapy (daily dose determined according to body weight, 8mg for bodyweight < 60 kg and 12 mg for bodyweight ≥ 60 kg) and will be discontinued 7 days before surgery.

The PD-1 inhibitor(sintilimab) is also started on the first day of radiotherapy, with a fixed dose of 200 mg every three weeks for three cycles. Surgery will be performed 6 to 8 weeks after radiotherapy (**Figure 2**). Dose adjustment, interruption, or discontinuation of lenvatinib and sintilimab according to the adverse events (AES) is detailed in **Tables 2**, **3**.

**Figure 2 f2:**
[figure not shown]
Clinical trial process.

**Table 2 T2:** Dose adjustment criteria of lenvatinib according to the AEs.

AEs	Degree of AEs	Management	Taper and resume lenvatinib mesylate
Hpertension	Grade 3 (despite optimal antihypertensive therapy)	Suspend	Remission to grade 0, 1 or 2.
	Grade 4	Permanently discontinue	Treatment must not be restarted
Pteinuria	≥ 2 g/24 hours	Suspend	Remission to less than 2g/24 hours
Nephrotic syndrome	-------	Permanently discontinue	Treatment must not be restarted
Renal insufficiency or kidney failure	Grade 3	Suspend	Remission to Grade 0-1 or Baseline
	Grade 4*	Permanently discontinue	Treatment must not be restarted
Heart dysfunction	Grade 3	Suspend	Remission to Grade 0-1 or baseline
	Grade 4	Permanently discontinue	Treatment must not be restarted
Posterior Reversible Encephalopathy Syndrome (PRES) / Reversible Posterior Leukoencephalopathy Syndrome (RPLS)	Any grade	Suspend	If remission reaches grade 0-1, consider restarting treatment at a reduced dose
Liver toxicity	Grade 3	Suspend	Remission to Grade 0-1 or baseline
	Grade 4*	Permanently discontinue	Treatment must not be restarted
Arterial thromboembolism	Any grade	Permanently discontinue	Treatment must not be restarted
Bleeding	Grade 3	Suspend	Remission to Grade 0-1
	Grade 4	Permanently discontinue	Treatment must not be restarted
Gastrointestinal perforation or gastrointestinal fistula	Grade 3	Suspend	Remission to Grade 0-1 or baseline
	Grade 4	Permanently discontinue	Treatment must not be restarted
Parenteral fistula	Grade 4	Permanently discontinue	Treatment must not be restarted
QT interval prolongation	>500 ms	Suspend	Remission to ≤ 480 ms or baseline
diarrhea	Grade 3	Suspend	Remission to Grade 0-1 or baseline
	Grade 4 (although medically managed)	Permanently discontinue	Treatment must not be restarted

* It can be treated according to Grade 3 adverse reactions if it is judged to be non-life-threatening when the adverse reaction is laboratory abnormal Grade 4.

**Table 3 T3:** Adjustment criteria of PD-1 inhibitor according to the AEs.

AEs	Degree of AEs	Management	Taper and resume lenvatinib mesylate
Pneumonia	Grade 2	Suspend	Remission to grade 0-1.
	Grade 3 or 4 or recurrent grade 2	Permanently discontinue	Treatment must not be restarted
Nephritis	Grade 2, creatinine greater than 1.5 times and less than 3 times of ULN	Suspend	Remission to grade 0-1.
	Grade 3 or 4, creatinine greater than 3 times of ULN	Permanently discontinue	Treatment must not be restarted
Colitis	Grade 2 or 3	Suspend	Remission to grade 0-1.
	Grade 4 or recurrent grade 3	Permanently discontinue	Treatment must not be restarted
Endocrine disease	Adrenal insufficiency Symptomatic hypophysitis Type 1 diabetes with hyperglycemia ≥ grade 3 (fasting blood glucose > 250 mg/ml or 13.9 mmol/L) or related ketoacidosis Hyperthyroidism ≥ grade 3	Suspend	Remission to Grade 0-1. For patients with grade 3 or 4 endocrine disease who have improved to grade 2 or lower, and who have clinical symptoms that can be controlled by hormone replacement, consider continuing PD-1 inhibitors after reducing the dose of corticosteroids, otherwise treatment should be discontinued. Hypothyroidism can be managed with replacement therapy without interruption of treatment.
Hepatitis	Grade 2, ALT or AST > 3-5 times ULN or TBIL > 1.5-3 times ULN	Suspend	Remission to Grade 0-1.
	Grade 3-4, ALT or AST > 5 times ULN or TBIL > 3 times ULN	Permanently discontinue	Treatment must not be restarted
Skin reaction	Grade 3 or suspected Stevens-Johnson syndrome (SJS) or toxic epidermal necrolysis (TEN)	Suspend	Remission to Grade 0-1.
	Grade 4 or confirmed SJS or TEN	Permanently discontinue	Treatment must not be restarted
Other immune-related adverse reactions	Depending on the severity and type of reaction, grade 2 or 3	Suspend	Remission to Grade 0-1 or baseline
	Grade 3 or 4 myocarditis Grade 3 or 4 encephalitis Grade 3 or 4 Guillain-Barre syndrome	Permanently discontinue	Treatment must not be restarted
	Grade 4 or recurrent grade 3	Permanently discontinue	Treatment must not be restarted
Infusion-related reactions	Grade 3 or 4	Permanently discontinue	Treatment must not be restarted

